## Abstract

**Background:**

Umbilical cord blood (UCB) is an important source of hematopoietic stem cells (HSCs). However, the concentration of cells in cord blood units is limited and this may represent the main restriction to their therapeutic clinical use. The percentage of metabolically active stem cells provides a measure of the viability of cells in an UCB sample. It follows that an active cellular metabolism causes a proliferation in stem cells, offering an opportunity to increase the cellular concentration. A high cell dose is essential when transplanting cord stem cells, guaranteeing, in the receiving patient, a successful outcome.

This study is designed to evaluate the impact of docosahexaenoic acid (DHA) supplementation in pregnant women, in order to increase the quantity and viability of the cells in UCB samples.

**Methods/design:**

The metabolic demand of DHA increases in the course of pregnancy and reaches maximum absorption during the third trimester of pregnancy. According to these observations, this trial will be divided into two different experimental groups: in the first group, participants will be enrolled from the 20th week of estimated stage of gestation, before the maximum absorption of DHA; while in the second group, enrolment will start from the 28th week of estimated stage of gestation, when the DHA request is higher. Participants in the trial will be divided and randomly assigned to the placebo group or to the experimental group. Each participant will receive a complete set of capsules of either placebo (250 mg of olive oil) or DHA (250 mg), to take one a day from the 20th or from the 28th week, up to the 40th week of estimated gestational age. Samples of venous blood will be taken from all participants before taking placebo or DHA, at the 20th or at the 28th week, and at the 37th to 38th week of pregnancy to monitor the level of DHA. Cell number and cellular viability will be evaluated by flow cytometry within 48 hours of the UCB sample collection.

**Trial registration:**

International Standard Randomised Controlled Trial Number Register: ISRCTN58396079. Registration date: 8 October 2013.

## Background

Umbilical cord blood (UCB) cells provide an alternative source of hematopoietic stem cells (HSCs) for those patients with hematologic diseases unable to find a fully compatible donor.

Over the last 25 years, the field of UCB banking and transplantation has grown exponentially [1]. However, despite the successes, one of the main problems with using UCB for transplantation is related to the reduced number of hematopoietic progenitor cells (HPCs) and HSCs compared with bone marrow or mobilized peripheral blood grafts.

The risk of graft failure increases with the limited number of available HPCs and HSCs, including delayed hematopoietic engraftment [2-4] and delayed immune reconstitution [5,6]. The studies show a cumulative incidence of nonengraftment that ranges from 10 to 20% after UCB transplantation, while the median time for neutrophil recovery is between 22 and 27 days.

Protocols on intravenous CD34+ stem cell transplants specify a minimum dose equivalent to 3 × 10^7^ mononuclear cells/kg of body weight and 1.5 × 10^5^ CD34+/kg of the patient’s weight at the time of the infusion. Umbilical cord collections are 11 × 10^8^ mononuclear total number of cells and 3 × 10^6^ CD34+, thus usually sufficient for a transplant in a 14-year-old child [7].

It is evident that it is necessary to increase the proliferative ability of stem cells in the UCB so that these cells are viable and sufficiently mature to engraft after transplant.

*In vitro* experiments showed that the viability of the HSCs, deriving from UCB, could be augmented with favourable effects on the engraftment potential [8,9]. These studies revealed that the beneficial effect of the *in vitro* generation of megakaryocytes from UCB, together with a higher ability to survive the cryopreservation, were observed when docosahexaenoic acid (DHA) and arachidonic acid (AA) were supplemented in the growth medium [8,9], increasing the clinical utility of the UCB [9]. In particular, DHA, which belongs to the polyunsaturated fatty acids (PUFAs) family, is a fundamental element of cell membranes [10,11], especially those of the brain and retina [12]. The chemical structure of DHA is illustrated in Figure 1. DHA accumulation in the brain and retina occurs mainly between the last intrauterine trimester and the initial months of life. The metabolic demand of DHA increases progressively in the course of pregnancy, particularly during the third trimester. In this phase a sudden acceleration of foetal growth is observed together with a great deposition of fatty acids in the central nervous system [13]. Therefore, the level of DHA during pregnancy can directly influence the stages of development [14]. Observational studies have also demonstrated a close association between the DHA availability during the perinatal period with long-term cognitive and visual development [15,16]. Besides, the consumption of large quantities of fish, rich in DHA, has been associated with an increase in gestational age, a greater foetal weight at birth and less incidence of pre-eclampsia [17,18].

**Figure 1 F1:**
[figure not shown]
Chemical structure of docosahexaenoic acid (DHA).

The effect of DHA on foetal weight and development is linked to its effect on the endothelium. DHA increases the flow of blood through vasodilatation in young adults and improves membrane receptor activity. Therefore, it is possible that these fatty acids improve foetal growth, increasing the placental flow by potentiating the activity of prostacyclin versus thromboxane and reducing blood viscosity [19].

Furthermore, treatment with DHA in the third trimester of the pregnancy improves the mother’s DHA status, as indicated by the composition of fatty acids in the maternal erythrocyte membrane [20-22].

However, it should be considered that, during the course of the third trimester, the foetus absorption of DHA is 70 to 100 mg from the maternal bloodstream daily; at the same time, during the second half of the pregnancy, the mother’s needs of DHA supplementation also grows to support the higher request from the foetus without any detrimental effect on her own reserves. Hence, during the third trimester, with an excess or greater availability of DHA, the foetus will tend to accumulate it preferentially in the brain tissue competing with the accumulation on the surface of other cells, specifically, HSCs.

In Denburg *et al*. [23], the effects of a supplementation with n-3 PUFA were assessed in a population of neonatal CD34+ cells as a method for preventing allergies. In this study, the pregnant women were treated, from the 20th week of gestation until delivery, with fish oil capsules or a placebo of olive oil capsules in a randomized control trial (RCT). The results revealed that, in the group given fish oil, the percentage of CD34+ present in the cord blood was greater than that found in the control group (0.879 ± 0.096 versus 0.533 ± 0.041; *P* <0.002) [23]. The study confirmed that a maternal dietary supplementation with n-3-PUFA increases the levels of these fatty acids in the infant’s cell membranes and this has a significant effect on the CD34+ cell population in the cord blood.

The aim of this study is to increase the viability of the stem cells collected at birth from the UCB, in particular of the haematopoietic lineage, by administrating purified DHA during the second (20th week of estimated gestational stage) or third (28th week of estimated gestational stage) trimester of pregnancy. The purified DHA consists of at least 250 mg/day derived from purified fish oil or from microalgae extraction administered to pregnant women orally in the form of capsules in a randomized, double-blind, monocentric study. The choice to administer 250 mg/day is prompted by the European Community’s recommended dose for treatment in pregnancy, based on the outcomes of the Perinatal Lipid Intake Working Group and the Early Nutrition Programming Project. This dose is sufficient to maintain maternal-foetal unity and satisfy the needs of both without incurring the risk of a deficiency in this nutrient.

In this trial, we hypothesize that a DHA supplementation, during the second or third trimester of pregnancy, can increase the metabolic activity of the stem cells in UCB samples overcoming the limit imposed by the extraction of cord blood. Indeed, unlike other sources, UCB cells have only one possibility of extraction, and it is thus essential that the cell product obtained is qualitatively and quantitatively sufficient for a transplant in adulthood. This treatment can also foster the engraftment of stem cells of the haematopoietic lineage after transplant, reducing the window period after transplantation in which haematopoietic stem cells must colonize the bone marrow, and specialize into cells of the circulatory system and of the immune system.

## Methods

### Recruitment

The trial is designed to target pregnant women within the 20th or 28th week of gestation. At the time of recruitment, the participants will sign an informed consent form, and complete a questionnaire authorizing third parties to obtain demographic, anamnestic and nutritional data. The information thus obtained will be entered into a case report form for each pregnant woman.

Detailed information on benefits and risks of DHA will be provided to study candidates. Participants that meet pre-specified eligibility criteria (Table 1) and provide written informed consent will be enrolled in the study.

**Table 1 T1:** Eligibility criteria

**Inclusion criteria**	**Exclusion criteria**
Caucasian	When it is impossible to collect cord blood (bureaucratic reasons or because of emergencies regarding the health of the mother or the baby)
Non-smokers	Women who have taken other supplements containing DHA or fish oil
Over 18 years of age	Mother with a temperature of 39°C during delivery
Single pregnancy	UCB samples with a volume of less than 80 ml and/or less than 70% cell vitality
Absence of diabetes or hypertension, or any other type of pathology requiring pharmacological therapy	
Absence of chromosome abnormalities and/or congenital malformations in the foetus	
HBV, HCV, HIV and CMV negative	

CMV, cytomegalovirus; DHA, docosahexaenoic acid; HBV, hepatitis B virus; HCV, hepatitis C virus; UCB, umbilical cord blood.

The Ethics Committee of the San Giovanni Calibita Fatebenefratelli Hospital (Rome, Italy), in compliance with the Helsinki Declaration, approved the study protocol (9 July 2009, reference: 35/2009; and 9 December 2010, reference: 67/2010). The trial is registered at the International Standard Randomised Controlled Trial Number Register (ISRCTN58396079).

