**Figure 2 F2:**
[figure not shown]
**Work flow for the study.** After recruitment the participants will be randomized into one of the two groups. Samples of venous blood will be taken from all participants before taking placebo or DHA (20th or 28th week) and at the 37th to 38th week of pregnancy to monitor the level of DHA. After birth, UCB samples will be collected and processed within 48 hours. DHA, docosahexaenoic acid; UCB, umbilical cord blood.

Each participant will receive a complete set of capsules of either placebo or DHA, to take one a day from the 20th or 28th week up to the 40th week of estimated gestational age. The placebo pills (placebo batch) will contain 250 mg of olive oil. This choice is conditioned by the need to use a product of proven safety with a consistency and flavour as similar as possible to fish oil.

The DHA capsules (active batch) will contain 250 mg of DHA (Incromega™ DHA 250TG SR, Croda, Goole, UK) + 10 mg natural vitamin E (Avantgarde sigma-tau, Rome, Italy). The DHA in the capsule is extracted from fish oil by PureMax™ technology (Croda) that enables lipids to be purified and concentrated to maximum standards. This ensures that the DHA used for this study is free of contaminants, including: heavy metals, such as mercury, arsenic, cadmium and lead; oxidant impurities; dioxins and furans; dioxin-type polychlorinated biphenyls; and polycyclic aromatic hydrocarbons.

The packaging of the capsules in the two groups will be identical (see Table 2).

**Table 2 T2:** Features of the DHA and placebo batch

**Feature**	**DHA**	**Placebo**
Tablet formulation	250 mg Incromega DHA + 10 mg natural vitamin E	250 mg olive oil
Capsule type	10 mm, oval shape	10 mm, oval shape
Capsule colour	Dark yellow	Dark yellow
Batch production	20,000 tablets	20,000 tablets
Size of the blisters	82 × 132 mm	82 × 132 mm
Blister per case	1	1
Number of tablets per blister	30	30
Packaging	White box	White box

DHA, docosahexaenoic acid.

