### Collection of cord blood

Before extracting the cord blood, the recruited pregnant women must carry out serological tests to prove the absence of the following infectious diseases: hepatitis B virus; hepatitis C virus; HIV; cytomegalovirus; human T-cell lymphotropic virus; and syphilis. The report will then be presented to the hospital to obtain the licence.

All the participants will receive a free cord blood collection kit provided by SmartBank (SmartBank, Rome, Italy). Hospital staff assisting the birth will immediately extract and collect the cord blood with the kit. Samples will be shipped to the Biovault technical laboratory (Plymouth, UK) for specific analysis of: volume (ml); pH; cell viability (%); number of CD34+ cells; number of leukocytes; and bacterial and viral tests. In order to determine the DHA percentage in the cord blood erythrocyte membranes, 2 cc of the extracted cord blood will be sent to the Lipinutragen-CNR laboratory in Bologna.

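### Excluding cord units below 80 ml or 70% viability selects on the trial's own result after randomisation and shrinks any real DHA effect

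*Protocol article*

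**What the plan says.** In the Recruitment section, Table 1 gives the eligibility criteria. Its exclusion column contains "UCB samples with a volume of less than 80 ml and/or less than 70% cell vitality", and the text above it says that women who meet the table and consent are enrolled.

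The timing is set out in the legend of Figure 2 (Study design): "After recruitment the participants will be randomized into one of the two groups", and later "After birth, UCB samples will be collected and processed within 48 hours". The Abstract adds that "Cell number and cellular viability will be evaluated by flow cytometry within 48 hours of the UCB sample collection".

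On what the trial is meant to show, the Background says "The aim of this study is to increase the viability of the stem cells collected at birth from the UCB". The Abstract describes supplementation "in order to increase the quantity and viability of the cells in UCB samples". Under Collection of cord blood, the laboratory results on each unit include "volume (ml); pH; cell viability (%); number of CD34+ cells; number of leukocytes".

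The Statistical analysis section compares each DHA group with its placebo group by Student's t-test and ANOVA at P < 0.05. It says nothing that brings excluded units back into the comparison.

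**The concern.** An eligibility rule should use only what is known before randomisation. This one uses two measurements made on the cord unit after up to 20 weeks of capsules (week 20 to week 40). One of them, viability, is what the trial sets out to change. The other, volume, multiplies cell concentration to give total cell number. The Background also offers a route by which treatment might change volume: "it is possible that these fatty acids improve foetal growth, increasing the placental flow".

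If the rule is followed, the groups compared are no longer the groups randomised. The arm with more poor units loses more of them, so its mean rises more and the difference narrows. An effect that consisted only of rescuing poor units would largely vanish. The practical question is whether DHA makes more cord units good enough to use, and a data set restricted to units that are already good enough cannot answer it.

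**Working it through.** **No figure to reproduce.** The article states no sample size, effect size, SD or proportion of units below either threshold. The only inputs from the document are the two cut-offs, 70% and 80 ml (Table 1). Every mean, SD and effect below is an assumption, shown over a range.

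**Method.** For a normal variable with parameters μ and σ, restricted to the interval from c to b, let A = (c − μ)/σ and B = (b − μ)/σ. Then

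E[X | c ≤ X ≤ b] = μ + σ·[φ(A) − φ(B)] / [Φ(B) − Φ(A)].

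Viability cannot exceed 100%, so b = 100. The true mean uses no lower cut; the analysed mean uses c = 70. For volume, b is infinite and c = 80.

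**Viability, one case in full: μ = 80 (placebo) and 85 (DHA), σ = 10.**

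- Placebo: A = −1, B = 2, φ(A) = 0.2420, φ(B) = 0.0540, Φ(A) = 0.1587, Φ(B) = 0.9772.
  - Mean of all units: 80 − 10 × 0.0540/0.9772 = 79.45.
  - Mean after exclusion: 80 + 10 × (0.2420 − 0.0540)/(0.9772 − 0.1587) = 82.30.
  - Removed: 0.1587/0.9772 = 16%.
- DHA: A = −1.5, B = 1.5, φ(A) = φ(B) = 0.1295, Φ(A) = 0.0668, Φ(B) = 0.9332.
  - Mean of all units: 85 − 10 × 0.1295/0.9332 = 83.61.
  - Mean after exclusion: 85.00.
  - Removed: 0.0668/0.9332 = 7%.
- True difference: 83.61 − 79.45 = 4.16 points. Analysed difference: 85.00 − 82.30 = 2.70 points, which is 65% of the truth.

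**Viability, range (shift of 5 in μ).**

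| Placebo μ, σ | True difference | Analysed difference | Share left | Removed, placebo / DHA |
|---|---|---|---|---|
| 75, 10 | 4.62 | 2.41 | 52% | 31% / 16% |
| 80, 10 | 4.16 | 2.70 | 65% | 16% / 7% |
| 85, 8 | 3.93 | 3.51 | 89% | 3.1% / 0.7% |
| 90, 8 | 3.06 | 2.94 | 96% | 0.7% / 0.1% |
| 90, 5 | 3.84 | 3.84 | 100% | about 0 / about 0 |

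Without the bound at 100%, the 80/10 case gives 3.51 out of 5.00, or 70%. The conclusion does not depend on the bound.

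**Volume (σ = 25 ml).** At μ = 90 against 100:

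- Placebo: A = −0.4, so the mean after exclusion is 90 + 25 × 0.3683/0.6554 = 104.05.
- DHA: A = −0.8, so it is 100 + 25 × 0.2897/0.7881 = 109.19.
- The true gain of 10 ml becomes 5.14 ml (51%), with 34% of placebo and 21% of DHA units removed.

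| Placebo mean | Share left, gain 5 ml | Share left, gain 10 ml |
|---|---|---|
| 80 | 39% | 41% |
| 90 | 49% | 51% |
| 100 | 60% | 63% |
| 120 | 82% | 84% |

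**Cell number.** I simulated total CD34+ as volume times concentration, with volume mean 90 ml and SD 25, and log-normal concentration with log-SD 0.5. A DHA effect acting only through volume (+10 ml) has a true ratio of 1.11, and 1.05 after the 80 ml cut. If log concentration also correlates −0.3 with volume, the cut creates a concentration ratio of 1.03 where the truth is 1.00.

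**No effect.** If DHA changes neither viability nor volume, both arms lose the same share and the difference stays at zero.

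**The case against.** Five points can be made for the plan.

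1. *The bias is conditional.* With no treatment effect on viability or volume there is none, and for those two variables it runs towards no difference, so it does not create a false positive there. This stands. It limits the harm to lost or understated effects, which still matters in a trial set up to find one.
2. *The viability cut may hardly bite.* If nearly all units exceed 70%, almost nothing is lost. This also stands: the document neither supports nor excludes a high failure rate. The 65% case needs 16% of placebo units to fail.
3. *Volume is not a named outcome.* It is a laboratory parameter and a component of quantity, and the step from placental flow to collected volume is an inference. The 39% to 63% range also reflects means placed close to the cut; at 120 ml, 82% to 84% survives. This stands as a limit on the volume part. The viability part is unaffected.
4. *The thresholds may be meant as unit-acceptance criteria.* That would justify not storing a unit. But the table calls them exclusion criteria, and no other section says such units stay in the analysis.
5. *The full protocol may define the analysis set.* It may, but this article fixes the rule as an exclusion, so an analysis of all randomised women elsewhere would contradict Table 1.

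**Conclusion.** The concern holds. As written, Table 1 conditions the DHA–placebo comparison on a post-randomisation measurement that is the trial's stated aim, and on a second one that determines cell quantity. Any real effect on viability or volume is attenuated. Under the assumed distributions the surviving share runs from about half to all of a viability effect, and from 39% to 84% of a volume effect with means of 80 to 120 ml. For CD34+ concentration the error can go either way. The size depends on how many units fall below the cut-offs, which the document does not report. The defect itself does not depend on that number: it follows from the order of randomisation, birth and measurement. It should be corrected before analysis.

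**What to change.** - Remove the volume and viability line from the exclusion criteria. If the thresholds are needed for storage, state them separately as banking criteria with no bearing on the analysis.
- Analyse every randomised woman from whom cord blood is collected, in her randomised arm, using the measured values.
- Add a secondary binary outcome, a unit of at least 80 ml with at least 70% viability, with all randomised women in the denominator and a stated rule for women with no collection.
- Report the number below each threshold by arm. Present the restricted set only as a labelled sensitivity analysis.
- The same column also excludes on maternal temperature during delivery and on cord blood that cannot be collected. Both arise after randomisation, so state how these women are counted in each arm.

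**Cost.** Volume and viability must be measured before the rule can be applied, so those two outcomes need no new data. The article does not say whether units below the thresholds receive the full CD34+ and leukocyte assays; that must be confirmed, and may add laboratory work. Recruitment is under way, so a change to the eligibility table probably needs an ethics amendment. Including poor units will somewhat increase the outcome variance.

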### Study design

Participants included in the trial will be divided into two groups: one group will be given the placebo; and the other group will be given DHA (Figure 2). The placebo or DHA will be assigned in a double-blind, randomized manner, created by a computer program producing a sequence of codes attributed to one of the two groups. An identifying code, assigning the woman to one of the two study groups, guarantees, from that moment on, anonymity in treating sensitive data.

**Figure 2 F2:**
[figure not shown]
**Work flow for the study.** After recruitment the participants will be randomized into one of the two groups. Samples of venous blood will be taken from all participants before taking placebo or DHA (20th or 28th week) and at the 37th to 38th week of pregnancy to monitor the level of DHA. After birth, UCB samples will be collected and processed within 48 hours. DHA, docosahexaenoic acid; UCB, umbilical cord blood.

Each participant will receive a complete set of capsules of either placebo or DHA, to take one a day from the 20th or 28th week up to the 40th week of estimated gestational age. The placebo pills (placebo batch) will contain 250 mg of olive oil. This choice is conditioned by the need to use a product of proven safety with a consistency and flavour as similar as possible to fish oil.

The DHA capsules (active batch) will contain 250 mg of DHA (Incromega™ DHA 250TG SR, Croda, Goole, UK) + 10 mg natural vitamin E (Avantgarde sigma-tau, Rome, Italy). The DHA in the capsule is extracted from fish oil by PureMax™ technology (Croda) that enables lipids to be purified and concentrated to maximum standards. This ensures that the DHA used for this study is free of contaminants, including: heavy metals, such as mercury, arsenic, cadmium and lead; oxidant impurities; dioxins and furans; dioxin-type polychlorinated biphenyls; and polycyclic aromatic hydrocarbons.

The packaging of the capsules in the two groups will be identical (see Table 2).

**Table 2 T2:** Features of the DHA and placebo batch

**Feature**	**DHA**	**Placebo**
Tablet formulation	250 mg Incromega DHA + 10 mg natural vitamin E	250 mg olive oil
Capsule type	10 mm, oval shape	10 mm, oval shape
Capsule colour	Dark yellow	Dark yellow
Batch production	20,000 tablets	20,000 tablets
Size of the blisters	82 × 132 mm	82 × 132 mm
Blister per case	1	1
Number of tablets per blister	30	30
Packaging	White box	White box

DHA, docosahexaenoic acid.

